Starting T cell dose within CIK cell infusions was 1x10^6 T cells/kg body weight. Regardless of donor type, dose escalation continued up to 1x10^8 T cells/kg body weight if no signs of acute GvHD >grade I occurred. Median doses of infused T cells were 6x10^7 in the matched unrelated and 1x10^7/kg in the haploidentical transplantation setting. Mild signs of acute GvHD occurred in 2 patients (14%).

Another 3 patients (21%) developed acute GvHD grade III with evidence of cutaneous, intestinal and hepatic involvement. All of these high-risk patients had been treated with CIK cells from haploidentical donors prophylactically at a maximum dose of 5x10^6, 5x10^6 and 20x10^6 CD3+CD56 CIK cells/kg body weight. All patients experienced a timely coincident regeneration of CD3+ T cells. Therefore it is not clear whether the occurrence of GvHD is solely attributable to CIK cell infusions. Treatment for acute GvHD included immunosuppressive medications in addition to steroid therapy and infusions of mesenchymal stroma cells. One patient additionally received extra corporal photopheresis. All patients finally recovered from GvHD and remained in complete remission until the last follow-up.

In 6 patients (43%), 3 with overt and 3 with impending relapse, CIK cell infusions temporarily provided stable disease (median 218 days, range 56-563 days), followed by another allogeneic SCT in 2 cases. Deaths of 2 heavily pretreated AML-patients (14%) who remained in remission after CIK cell infusions were not CIK cell-related. Another 6 leukemia patients (43%), 3 of whom were not in remission at the time of SCT, are still in complete remission. All of them were offered CIK cell infusions from haploidentical donors.

Accordingly, Introna, Laport, Linn and colleges described application of donor-derived CIK cells in adult patients with relapsed hematological malignancies after allogeneic SCT. Altogether, serial CIK cell infusions seem to be a promising therapeutic approach for patients being at risk of relapse, provided that CIK cells are administered in high numbers and short-term intervals, early after allogeneic SCT.

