### **Exploratory Endpoints**

Efficacy:

- Proportion of patients that achieve complete and partial response after 1 year of first CIK cells infusion.
- Progression-free survival and overall survival
- Response duration

Safety Endpoint:

- Proportion of patients who become aGvHD > grade II or extensive chronic GvHD.

CIK cells infusions:

- The dose-limiting toxicity based on grade III or IV acute GvHD

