## Confidence intervals for efficacy

To assess the efficacy of CIK cell treatment we consider the rate of patients who achieve a complete/partial molecular response following CIK cell infusion.

The two sided 95% confidence intervals for complete/partial molecular response rate from 5% - 50% for a sample size = 40 are

| Rate | Lower Limit | Upper limit | CI Width |
|------|-------------|-------------|----------|
| 0.05 | 0.006       | 0.163       | 0.163    |
| 0.1  | 0.028       | 0.237       | 0.209    |
| 0.2  | 0.091       | 0.356       | 0.266    |
| 0.3  | 0.166       | 0.465       | 0.300    |
| 0.4  | 0.249       | 0.567       | 0.318    |
| 0.5  | 0.338       | 0.662       | 0.324    |

The two sided 95% confidence intervals for the rate (5% - 50%) for patients that achieved complete/partial molecular response for a sample size = 20 are

| Rate | Lower Limit | Upper limit | CI Width |
|------|-------------|-------------|----------|
| 0.05 | 0.001       | 0.249       | 0.247    |
| 0.1  | 0.012       | 0.317       | 0.305    |
| 0.2  | 0.057       | 0.437       | 0.379    |
| 0.3  | 0.119       | 0.543       | 0.424    |
| 0.4  | 0.191       | 0.639       | 0.448    |
| 0.5  | 0.271       | 0.728       | 0.456    |

The following figure illustrates the CI width for different complete/partial molecular response rate for all patients (sample size = 40) and for each group (sample size = 20) with a two-sided confidence level equal to 95%.

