## Analysis

A descriptive statistics will be performed at the end of the study. An intent-to-treat principle (ITT) or per-protocol analysis will be done.

To analyze the efficacy of CIK cell treatment following factors will be considered:

- Complete and partial molecular response
- rate and duration of complete/partial molecular response following CIK cell administration at the end of CIK cell infusions and after 1 year of first CIK cell infusion
- rate of and time to non response
- rate of and time to relapse with previous partial/complete response
- Progression-Free survival (PFS) and overall survival (OS)
- Cumulative incidences of: haematological relapse/progression, deaths without relapse/progression
- Cumulative incidence of aGVHD > grade II and extensive chronic GvHD
- Median and range for the number of CIK cell dose and for cumulative dose CIK cells/kg for all patients, children and adults

- Median and range for cumulative T cells/kg according donor type (MSD, MUD,MMFD) that patient requires in the study

Complete molecular response is defined as the molecular remission: the Minimal Residual Disease not detectable (MRD < 10^-6) and Mixed Chimerism MC < 1%.

Partial response is defined as no molecular remission but not haematological relapse. Non response is defined as haematological relapse without previous or complete response.

The median of PFS and OS time will be estimated. Kaplan-Meier estimates will be used to estimate PFS probability and OS probability. Log-rank test will be used as appropriate. For PFS will be considered as events: disease progression or relapse, death without relapse/progression and secondary neoplasm. For OS death from any cause will be considered an event.

Gray-Model will be used for cumulative incidences. Patients lost to follow-up without event will be censored at the date of their last follow up evaluation.

PFS, OS and cumulative incidences will be estimated after 1 year initiation of CIK cell therapy and after 1 year until the last CIK cell infusion.

If the data meet the necessary requirements, longitudinal analysis will be conducted to explore the improvement of hematologic and immune reconstitution of leucocyte, CD3-, CD4-, CD8-, CD56-, and CD14-positive cells until the first year after begin of the CIK cells therapy.

The dynamic of cytokine profile during cell infusion and tumor escape mechanisms following CIK cell infusion will exhibit in curves over the time.

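### Death is missing from the response categories: a patient who dies without haematological relapse and without molecular remission is counted as a partial response and never as a non-response

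*Protocol*

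**What the plan says.** The Analysis part of protocol section 11 sets three response categories.

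- Complete: "Complete molecular response is defined as the molecular remission: the Minimal Residual Disease not detectable", with mixed chimerism below 1%.
- Partial: "Partial response is defined as no molecular remission but not haematological relapse".
- None: "Non response is defined as haematological relapse without previous or complete response".

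The first two are pooled for efficacy. Exploratory Endpoints lists "Proportion of patients that achieve complete and partial response after 1 year of first CIK cells infusion", and the precision argument says "we consider the rate of patients who achieve a complete/partial molecular response following CIK cell infusion". The Analysis list adds the response rate at the end of infusions, response duration, the rate of and time to non-response, and, as a separate item, relapse after a previous response.

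Death without relapse does appear in the same part of section 11, but only for other measures. The PFS events are "disease progression or relapse, death without relapse/progression and secondary neoplasm", and the competing-risk analysis covers "Cumulative incidences of: haematological relapse/progression, deaths without relapse/progression".

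**The concern.** The authors foresaw death without relapse and gave it a place in PFS and in the cumulative incidences, but not in the response categories. Take a patient who enters with mixed chimerism of 3%, develops severe acute GvHD after the second infusion, and dies at week 10 with neither molecular remission nor relapse. The three definitions label this patient a partial response.

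Such deaths are foreseeable. Section 6.1 lists death from infection after transplantation among the events to be anticipated. Section 8.1 stops infusions for GvHD above grade II or severe infection but keeps those patients in the study, and so in the response analysis.

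The pooled rate is the measure by which section 11 judges the sample sizes of 40 and 20, and the trial is meant to inform a larger study. A rate that counts some deaths as successes is a poor basis for that.

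**Working it through.** **1. The plan's own figure.** The intervals in section 11 are exact (Clopper-Pearson): lower limit = Beta quantile at 0.025 with parameters (x, n-x+1); upper limit = Beta quantile at 0.975 with parameters (x+1, n-x).

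- x=16, n=40: 0.249 to 0.567, width 0.318, as printed.
- x=8, n=20: 0.191 to 0.639, width 0.448, as printed.

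**2. The printed rules applied to each outcome.**

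| Molecular remission | Haematological relapse | Alive or dead | Category as printed |
|---|---|---|---|
| no | no | alive | partial |
| no | no | dead | partial |
| yes | no | dead | complete |
| no | yes | either | non-response |

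Vital status never changes the category. No death without relapse can be a non-response.

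**3. Size per death.** Reclassifying one death changes the pooled rate by 1/40 = 2.5 points overall, or 1/20 = 5 points in one age group.

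**4. Illustrative totals.** The protocol gives no rate for death without relapse and without molecular remission, so the number d is assumed. Start from an observed 40% that includes d such deaths, and compute (x-d)/n.

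| n | d | Rate with deaths as failures | Exact 95% CI |
|---|---|---|---|
| 40 | 0 | 16/40 = 40% | 24.9-56.7% |
| 40 | 2 | 14/40 = 35% | 20.6-51.7% |
| 40 | 4 | 12/40 = 30% | 16.6-46.5% |
| 40 | 6 | 10/40 = 25% | 12.7-41.2% |
| 20 | 0 | 8/20 = 40% | 19.1-63.9% |
| 20 | 1 | 7/20 = 35% | 15.4-59.2% |
| 20 | 2 | 6/20 = 30% | 11.9-54.3% |
| 20 | 3 | 5/20 = 25% | 8.7-49.1% |

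**5. Which definition causes what.** Suppose only partial response were repaired, so that it required a marker fall. With d=4 deaths and no such fall, the response rate would already be 12/40. Those four patients would then belong to no category, and the non-response rate would still omit 4/40 = 10 points. The inflated response rate therefore comes from the residual wording of partial response. The understated non-response rate comes from the relapse-only wording of non-response. Both sentences need changing.

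**The case against.** The strongest reply is that death does not create the misclassification. A living patient with unchanged markers and no relapse is also a partial response, so the inflated response rate belongs to the residual definition. This stands, as step 5 shows. It does not remove the point, because repairing partial response alone leaves these deaths outside non-response.

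Second, the deaths are analysed elsewhere, the study is declared explorative, the primary endpoints are GvHD, and no decision rule uses the response rate. This also stands and limits the severity. The sample size and the tabulated widths do not depend on the classification.

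Third, scoring of early deaths is often left to an SAP. Here, however, the protocol itself fixes the categories, and an SAP that followed them would repeat the result. The protocol names no method for time to non-response, so how these deaths would be handled there cannot be said with certainty; as defined, they are not events.

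Two stronger readings are tempting but unsupported.

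- A reader might take the pilot series as evidence of how often this happens. Section 1.5 reports: "Deaths of 2 heavily pretreated AML-patients (14%) who remained in remission after CIK cell infusions were not CIK cell-related". Those patients were in remission. The section does not say whether that was molecular; if it was, the printed rules make them complete responses. The series documents no clear case of death without both relapse and molecular remission, so 2/14 cannot supply the rate.
- A reader might infer that a more toxic product would look more effective. That holds only where death pre-empts a relapse. A patient who would otherwise have stayed relapse-free counts as a response dead or alive. Section 1.5 also reports that all three patients with grade III acute GvHD recovered.

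**Conclusion.** The point holds within limits. On the printed definitions, death without relapse and without molecular remission counts as a partial response, and death in molecular remission counts as a complete response. Neither can be a non-response. The size is 2.5 points per death at n=40 and 5 points at n=20. Any total rests on an assumed number of deaths; four of 16 apparent responders would take 40% to 30%.

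The error touches the complete, partial and non-response rates and the times built on them. It does not reach PFS, OS or the cumulative incidence of death without relapse, and it is no argument against the sample size. It should be corrected because it is a stated rule with a wrong result on the trial's chosen efficacy rate.

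**What to change.** Reword section 11 as follows.

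1. For the response proportion at each stated time point (end of infusions, 1 year after first infusion), a patient who died before that point is a failure and stays in the denominator of whichever analysis set is used. Tie the end-of-infusions time point to a dated assessment, such as the first follow-up after the last infusion, so that death before it is well defined.
2. Define non-response as haematological relapse, or death from any cause, without a previously documented complete or partial response. This keeps it distinct from the separately listed relapse after previous response.
3. In time to non-response, count such deaths as events. Treat death without relapse as a competing event only for the relapse-specific times.
4. Make partial response require a documented reduction in MRD or MC in a living patient; otherwise the residual wording still absorbs these cases. A living, relapse-free patient without such a reduction then needs a named category that does not count as response.

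A patient who responded and then died before 1 year is a failure in the 1-year proportion but not a non-response. Section 11 should say so, because the two rates will not sum to 100%.

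The change is to wording. Deaths are already collected for PFS and OS, and competing-risk methods are already planned. Visits and sample size stay as they are. The downside is a less favourable reported response rate.

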### **2.2 Secondary Objectives**

To assess the efficacy of CIK cell treatment based on:

- Reduction or disappearance of MRD
  - Achievement of complete donor chimerism,
  - Rate of and time to hematologic relapse in patients enrolled based on MRD and/or mixed chimerism
  - Progression-free and overall survival
- Molecular relapse will be assessed by STR and RT-PCR based chimerism analyses in all patients, by real time (RT)-PCR based BCR-ABL/ABL, or immunoglobulin (Ig)/T cell receptor (TCR) gene rearrangements in leukemia patients

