### **5.4 CIK Cell Recipient**

Patients with molecular relapse without aGvHD  $\geq$  grade II can be included and will receive CIK cell infusions in increasing doses.

Starting dose of  $1 \times 10^6$  CD3 $^{+}$ CD56 $^{-}$  CIK cells/kg recipient body weight will be increased in intervals of 4-6 weeks to  $5 \times 10^6$  CD3 $^{+}$ CD56 $^{-}$ , and  $1 \times 10^7$  CD3 $^{+}$ CD56 $^{-}$  CIK cells/kg. Patients will be screened for relapse and signs of GvHD according to GSC. Relapsed patients will be censored. Patients who experience disease progression or  $<$  grade II aGvHD may receive modified CIK cell doses. No further CIK cell infusions will be administered in the presence of aGvHD  $>$  grade II.

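### A patient whose molecular marker is rising counts as a partial responder, and the unqualified PFS event may count the same patient as a failure

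*Protocol*

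**What the plan says.** Section 11, Analysis, sets three response categories.

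- Complete: "Complete molecular response is defined as the molecular remission: the Minimal Residual Disease not detectable", together with mixed chimerism below 1%.
- Partial: "Partial response is defined as no molecular remission but not haematological relapse".
- None: "Non response is defined as haematological relapse without previous or complete response".

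Under the heading on confidence intervals for efficacy, section 11 takes the combined complete and partial molecular response rate as its efficacy measure and bases the precision tables on it.

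For PFS the same section says "For PFS will be considered as events: disease progression or relapse, death without relapse/progression and secondary neoplasm". Its list of cumulative incidences reads "Cumulative incidences of: haematological relapse/progression, deaths without relapse/progression". A further item, on rate of and time to relapse after an earlier response, uses relapse without a qualifier. Section 2.2 names "Rate of and time to hematologic relapse in patients enrolled based on MRD and/or mixed chimerism" as one objective and lists PFS as another.

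Section 5.4 handles the two states separately. It says "Relapsed patients will be censored", and then opens its provision on modified doses with "Patients who experience disease progression or".

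**The concern.** Every patient enters in molecular relapse but in haematological remission. Marker movement short of overt relapse is therefore a central outcome of this trial. The partial-response rule ignores its direction: falling, flat and rising markers all score alike. The response rate then mixes benefit with failure, and so does response duration, because a marker rise does not end a partial response.

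PFS is a named secondary endpoint and depends on the same boundary. If progression can be molecular, the section gives opposite verdicts on one patient at one visit. If it cannot, the text should say so, because an analyst can now find support for either reading and could choose after seeing the data.

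**Working it through.** **Plan's own figure.** Exact (Clopper-Pearson) 95% limits at a response rate of 0.4:

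- 16/40 gives 0.249 to 0.567, width 0.318 (stated: 0.318).
- 8/20 gives 0.191 to 0.639, width 0.448 (stated: 0.448).

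The arithmetic at this rate is right. The problem is what counts as a response.

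**Status at entry.** Section 4.1 requires detectable MRD, a BCR-ABL/ABL ratio of at least 10⁻⁴, or confirmed mixed chimerism of at least 1%. Section 4.3 admits patients in molecular relapse who are still in haematological remission. Such a patient has no molecular remission and no haematological relapse, so the partial-response condition is met before the first infusion.

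**Rules side by side, at a single assessment.**

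| State | Response rule | PFS if progression is haematological | PFS if progression includes molecular worsening |
|---|---|---|---|
| Molecular remission | complete | no event | no event |
| Marker falling, not cleared | partial | no event | no event |
| Marker unchanged | partial | no event | no event |
| Confirmed marker rise, no haematological relapse | partial | no event | **event** |
| Haematological relapse, no earlier response | none | event | event |

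The fourth row carries the point. Its response entry is wrong on either reading of PFS. The clash with PFS arises only in the last column.

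**Which column applies?** The cumulative-incidence item supports the haematological column. Section 5.4 supports the molecular one, since a patient who has progressed may still be dosed while a relapsed patient is handled separately. The PFS sentence itself carries no qualifier. In the item on relapse after response, a molecular meaning makes little sense for a partial responder, who by definition never left molecular relapse.

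**Size of the effect on the response rate.** Each reclassified patient moves the rate by 1/N: 1/40 = 0.025 overall and 1/20 = 0.05 within one age group. The documents give no number of such patients. Suppose, as an assumption, that k of the patients counted at a rate of 0.4 have a confirmed marker rise:

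| N | k | Rate after removal | Exact 95% CI |
|---|---|---|---|
| 40 | 0 | 16/40 = 0.40 | 0.249–0.567 |
| 40 | 2 | 14/40 = 0.35 | 0.206–0.517 |
| 40 | 4 | 12/40 = 0.30 | 0.166–0.465 |
| 40 | 8 | 8/40 = 0.20 | 0.091–0.356 |
| 20 | 0 | 8/20 = 0.40 | 0.191–0.639 |
| 20 | 2 | 6/20 = 0.30 | 0.119–0.543 |
| 20 | 4 | 4/20 = 0.20 | 0.057–0.437 |

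**The case against.** The strongest reply is that PFS is already haematological when section 11 is read as a whole. The cumulative-incidence item attaches that word to relapse/progression and then repeats the pair without it as shorthand. The PFS sentence reuses the shorthand. Section 5.4 concerns dosing and defines no endpoint. This is a fair reading and may be the intended one. It removes the clash with PFS, so the clash can only be stated conditionally. It does nothing for the response rule, which still scores a rising marker as a response.

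A second reply is that the study is exploratory and descriptive, and that detailed event definitions belong in the SAP. That holds for thresholds and confirmation rules, whose absence is not criticised here. It does not cover a response category that the protocol itself fixes. An SAP with a stricter category would depart from the protocol, and one that read progression as molecular would collide with it.

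Third, response followed later by failure is normal, and the plan provides for it. This stands: only dual status at the same assessment is a contradiction, and patients in molecular remission are complete responders who fall outside the point.

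**Conclusion.** The point holds in two parts of different strength. Without condition, the partial-response rule counts confirmed molecular worsening as a success and so inflates the efficacy rate by 2.5 points per such patient at N = 40 and 5 points at N = 20. The total is unknown, because the number of such patients is not in the documents. Conditionally, if progression includes molecular worsening, the same patient is a responder and a PFS failure at once.

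Three stronger inferences are not supported.

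- A reader might infer that the protocol certainly double-classifies patients. The haematological wording in the cumulative-incidence item leaves room for the other reading.
- A reader might expect that, once progression is haematological, 1 − PFS equals the sum of the two listed cumulative incidences. It need not, because PFS also counts secondary neoplasm, which neither incidence includes.
- A reader might try to state how far PFS would shift. No rate of molecular-only worsening is given, so any such figure would merely restate an assumption.

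For an exploratory study this should be corrected, but it does not undermine the design.

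**What to change.** In section 11, Analysis:

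1. State that a patient with a confirmed marker rise is not a partial responder.
2. Use one relapse/progression event, haematological as in the cumulative-incidence item, for PFS, for the cumulative incidence, and for time to relapse after an earlier response. Keep secondary neoplasm as a separate PFS event.

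Confirmed molecular worsening can be reported descriptively from samples already taken. It should not become a formal endpoint on the present schedule: after the last infusion, section 3.2 makes blood chimerism obligatory but leaves bone marrow, including MRD and BCR-ABL, optional. Ascertainment would be uneven for patients enrolled on those markers.

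The change is one of wording and needs no new visits or samples. Its price is a less favourable response rate and a PFS less sensitive to early molecular failure, which the descriptive report partly offsets.

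Separately, sections 3, 3.2 and 3.3 end infusions when the patient progresses, whereas section 5.4 allows modified doses on progression. These contradict each other and the sponsor must reconcile them. No clinical rule is proposed here, and the analysis definition above is not meant to settle that question.

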### **2.1 Primary Objectives**

- To assess the safety and feasibility of increasing cell doses of CIK cell transfusions in adult and pediatric leukemia and MDS patients with molecular relapse after allogeneic SCT. The occurrence of grade III or IV acute GvHD and extensive chronic GvHD will be judged being related to the CIK cell intervention. Grading and staging will be performed using the Glucksberg Seattle scale.

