### **3.3 Study Duration**

The estimated duration of the recruitment period will be 3 years and the total duration of the study is expected to be at least 5 years.

The study duration per patient will include study phase during CIK cell infusions and observational phase after the last CIK cell infusion.

Study phase will last until the patient reaches molecular remission (= end of CIK cell infusions), progresses or until the patient has received a maximum of 8 CIK cell infusions (maximum duration of study phase 1 year).

Observational phase will last 1 year after the last CIK cell infusion.

Additionally, CIK cell infusions will be terminated if the patient meets discontinuation criteria (see chapter 8.1). "Off-protocol" patients will be followed up for another 28 days. Patients where CIK cell infusions are discontinued, but who stay in the protocol will be followed up for 1 year (see chapter 8.1).

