**The following criteria lead to withdrawal from study; patients will be followed up for one month:**

- Pregnancy of female patients
- Relapse of the underlying disease during CIK cell treatment requiring other treatment (e.g. systemic chemotherapy, second stem cell transplantation)

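### GvHD and 1-year complete response arising after a later DLI, transplant or chemotherapy are attributed to CIK cells, because the counting rules do not stop at the start of new therapy

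*Protocol*

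**What the plan says.** **Safety.** Section 2.1 states: "The occurrence of grade III or IV acute GvHD and extensive chronic GvHD will be judged being related to the CIK cell intervention". It sets no time limit and makes no exception for other therapy. Section 11 then plans the proportion and the cumulative incidence of aGvHD above grade II and extensive cGvHD, again without a condition on intervening treatment.

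**Response.** Section 11, Exploratory Endpoints, lists: "Proportion of patients that achieve complete and partial response after 1 year of first CIK cells infusion". Under Analysis, complete response rests on MRD and chimerism levels alone. For the rest: "Partial response is defined as no molecular remission but not haematological relapse". Response is also assessed at the end of the infusions.

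**PFS and censoring.** The event list is: "For PFS will be considered as events: disease progression or relapse, death without relapse/progression and secondary neoplasm". The censoring rule in that section is: "Patients lost to follow-up without event will be censored at the date of their last follow up evaluation".

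**Who stays in follow-up.** Infusions stop after the eighth without remission (section 3.1), or for GvHD above grade II, severe infection or response, with the patient remaining in the study (section 8.1). Section 3.3 adds: "Patients where CIK cell infusions are discontinued, but who stay in the protocol will be followed up for 1 year".

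**Limits on other therapy.** Section 4.3 bars concomitant antineoplastic treatment other than a TKI in BCR-ABL positive disease. Section 3.2 makes absence of chemo- or immune therapy a condition for the next infusion. Section 8.1 requires withdrawal, with one month of follow-up, for: "Relapse of the underlying disease during CIK cell treatment requiring other treatment". It also lets the investigator withdraw a patient for treatment failure or other reasons.

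**The concern.** The limits on other therapy apply while infusions continue. None reaches the year after the last infusion, where DLI or a second transplant is most likely. Section 5.5 says that at-risk patients always relapse without further treatment, and it names pre-emptive immunotherapy and second transplant as their only chance of cure. A patient with persistent MRD or mixed chimerism after the eighth infusion is the natural candidate for either.

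The trial has no control arm, so nothing separates the effect of the later therapy from that of CIK cells. A marker cleared by a second graft counts as a CIK complete response. GvHD caused by DLI enters the CIK GvHD rate, which section 11 sets against a 40% DLI rate with the expectation that CIK will be lower. That blurs the contrast the safety analysis is meant to show, and it does so largely through patients in whom CIK did not succeed.

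**Working it through.** **1. The plan's own figure.** For 16 responders among 40, the exact (Clopper-Pearson) 95% limits are Beta(0.025; 16, 25) = 0.249 and Beta(0.975; 17, 24) = 0.567. The width is 0.318, as printed in section 11, and the half-width is 0.159. It serves as a yardstick below.

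**2. Time at risk.** Eight infusions have seven intervals of 4 to 6 weeks, so the last falls at week 7 × 4 = 28 to 7 × 6 = 42. New therapy then has 52 − 42 = 10 to 52 − 28 = 24 weeks to act before the 1-year response assessment, and longer if infusions stop early. For GvHD the window is the whole observational year.

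**3. Routes and endpoints.** This takes section 11's PFS definition as governing. Section 5.4 says that relapsed patients are censored, which conflicts with relapse as a PFS event and must be reconciled.

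| Route to new therapy | PFS | 1-year complete response | GvHD |
|---|---|---|---|
| Relapse during CIK treatment needing other therapy | event already counted | largely closed by withdrawal | about one month exposed |
| Relapse after last infusion, then therapy | event already counted | exposed if relapse and clearance both fall before 1 year | exposed |
| No relapse; infusions stopped | exposed | exposed | exposed |

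In the last row, a patient with persistent MRD is already a partial responder. Clearance moves that patient from partial to complete. The combined rate changes only if the therapy averted a relapse before one year.

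**4. How many patients.** The documents give no rate of later therapy without relapse. The nearest figure is in section 1.5, where temporary stable disease was "followed by another allogeneic SCT in 2 cases". That is 2/14 = 14.3% (exact 95% CI 1.8% to 42.8%), and 0.143 × 40 = 5.7. I assume a range of 3 to 9 of 40 around this.

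**5. GvHD.** Extra events = k × 0.40, with 0.40 the protocol's DLI figure for aGvHD above grade II:
- k = 3: 1.2 events, 1.2/40 = 3 points
- k = 6: 2.4 events, 6 points
- k = 9: 3.6 events, 9 points

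This assumes that none of the k already had a severe event. Allowing independent overlap, observed rate = p + (1 − p) × (k/40) × 0.40. A true 10% then reads as 12.7%, 15.4% or 18.1%, and a true 20% as 22.4%, 24.8% or 27.2%.

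**6. Complete response.** Each later-treated patient who clears the marker and is counted adds 1/40 = 2.5 points. If m of them clear it, the rise is 2.5 × m points. With m = 6 the rise is 15 points, close to the 0.159 half-width, but that needs all six to clear. The protocol puts success of a second transplant at no more than 20%. That is not a marker-clearance rate, but as a lower illustration 6 × 0.20 = 1.2 patients, or 3 points.

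**The case against.** - **Later therapy is not ignored.** A reader might infer from section 11 that it is. That goes too far. Concomitant therapy is barred, relapse during treatment needing rescue means withdrawal, and section 8.1 allows discretionary withdrawal for treatment failure. This stands, but discretion is not a counting rule, and patients in the observational phase are expressly kept in the study.
- **PFS is not generally inflated.** Where relapse comes first, the event precedes the rescue. This stands, and it confines the PFS issue to therapy begun without relapse. Following patients regardless of later therapy is also a legitimate estimand, so the current PFS definition need not be replaced.
- **The sizing endpoint barely moves.** The confidence intervals in section 11 are for complete/partial response, and end-of-infusion response largely precedes later therapy. Both stand. The exposed figures are 1-year complete response and response duration.
- **A shift from 20% to 35% is a worst case.** One could assume 8 true complete responses and 6 later clearances, giving 14/40. The documents do not support this as an estimate. The two transplants came from a group of three overt and three impending relapses, and the text does not say whether they had progressed first.
- **Overstating GvHD is cautious.** True for protection of patients, but not for a comparison with a DLI rate when the added events come from DLI or a second graft. The 40% is also a DLI figure, while the patient count is drawn from transplants, so step 5 is only illustrative.
- **The sentence in 2.1 may mean that relatedness will be assessed.** Possible, but section 11 counts GvHD without any relatedness condition.
- **A statistical analysis plan might add rules.** It might, but the protocol itself fixes the attribution sentence, the response definitions and the PFS event list.

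**Conclusion.** The point holds for two groups. The first is patients without haematological relapse who stop CIK infusions and then receive DLI, a further transplant or other systemic anti-leukaemic therapy in the observational year: complete response, response duration, PFS and GvHD are all exposed. The second is any patient with GvHD after later therapy, including therapy for relapse after the last infusion.

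The number affected cannot be derived from the documents. Under an assumed 3 to 9 of 40 patients and the 40% DLI risk, about 1 to 4 GvHD events (3 to 9 percentage points, slightly less with overlap) would be charged to CIK cells. Complete response at 1 year rises by 2.5 points per patient who clears the marker. The study is exploratory and no test decision hangs on this, but one of the affected figures is the primary safety endpoint of an uncontrolled trial. If start dates of new therapy are not recorded, the analysis cannot separate the two effects afterwards.

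**What to change.** - Record the start date and type of any new anti-leukaemic therapy other than a TKI taken at entry.
- In 2.1 and section 11, count the primary GvHD endpoint up to that start. Treat the start as a competing event in the cumulative incidence, for which a Gray model is already planned, and list later GvHD separately.
- Count such patients as not in CIK response at later time points, end response duration at that date, and keep any response documented earlier.
- Keep the current PFS definition and add a sensitivity analysis that counts the start of new therapy as an event. OS stays all-cause.
- Reconcile the censoring statement in section 5.4 with the PFS event list.

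These are counting rules and change no treatment. The cost is protocol wording, one extra data item, and somewhat less favourable 1-year complete response figures.
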